# Early pathophysiology-driven airway pressure release ventilation versus low tidal volume ventilation strategy for patients with moderate-severe ARDS: study protocol for a randomized, multicenter, controlled trial

**DOI:** 10.1186/s12890-024-03065-y

**Published:** 2024-05-23

**Keywords:** Acute respiratory syndrome distress, Airway pressure release ventilation, Low tidal volume, Mechanical ventilation, Randomized controlled trial

## Abstract

**Background:**

Conventional Mechanical ventilation modes used for individuals suffering from acute respiratory distress syndrome have the potential to exacerbate lung injury through regional alveolar overinflation and/or repetitive alveolar collapse with shearing, known as atelectrauma. Animal studies have demonstrated that airway pressure release ventilation (APRV) offers distinct advantages over conventional mechanical ventilation modes. However, the methodologies for implementing APRV vary widely, and the findings from clinical studies remain controversial. This study (APRVplus trial), aims to assess the impact of an early pathophysiology-driven APRV ventilation approach compared to a low tidal volume ventilation (LTV) strategy on the prognosis of patients with moderate to severe ARDS.

**Methods:**

The APRVplus trial is a prospective, multicenter, randomized clinical trial, building upon our prior single-center study, to enroll 840 patients from at least 35 hospitals in China. This investigation plans to compare the early pathophysiology-driven APRV ventilation approach with the control intervention of LTV lung-protective ventilation.

The primary outcome measure will be all-cause mortality at 28 days after randomization in the intensive care units (ICU). Secondary outcome measures will include assessments of oxygenation, and physiology parameters at baseline, as well as on days 1, 2, and 3. Additionally, clinical outcomes such as ventilator-free days at 28 days, duration of ICU and hospital stay, ICU and hospital mortality, and the occurrence of adverse events will be evaluated.

**Trial ethics and dissemination:**

The research project has obtained approval from the Ethics Committee of West China Hospital of Sichuan University (2019-337). Informed consent is required. The results will be submitted for publication in a peer-reviewed journal and presented at one or more scientific conferences.

**Trial registration:**

The study was registered at Clinical Trials.gov (NCT03549910) on June 8, 2018.

**Supplementary Information:**

The online version contains supplementary material available at 10.1186/s12890-024-03065-y.

## Introduction

Mechanical ventilation is a crucial component of the treatment of acute respiratory distress syndrome (ARDS) [1]. However, it has the potential to exacerbate lung injury through regional alveolar overinflation and/or repetitive alveolar collapse with shearing (atelectrauma) [2, 3]. In the conventional lung-protective ventilation strategy, achieving a balance between recruitment and over-distension is challenging due to the diverse lesion areas that require different pressures for reopening and have varying critical closing pressures for individual patients [4, 5]. Despite the development of numerous mechanical ventilation strategies over the past two decades, mortality rates for patients with moderate to severe ARDS remain unacceptably high, reaching 40–50% [6, 7].

Most mechanical ventilation strategies aimed at mitigating ventilator-induced lung injury (VILI) operate under the assumption that alveoli behave elastically, reaching an elastic load limit based on elastin/collagen interaction [8]. However, in reality, alveoli function as a viscoelastic system, exhibiting a lag between the onset or removal of stress and the initiation of volume change [9, 10]. From an anatomical standpoint, it is crucial to consider the presence of collateral respiratory pathways, such as the pores of Kohn, interalveolar septal pores, and canals of Lambert, which provide additional connections between adjacent alveoli, facilitating the redistribution of alveolar volume and pressure throughout the lung over time [11, 12]. This process promotes uniform ventilation and gas exchange within the lungs. Previous studies have indicated that alveolar recruitment and collapse not only rely on the magnitude of pressure applied to the lung but also on the duration for which the pressure is applied [13–15].

Considering the viscoelastic nature of the lung in ARDS, airway pressure release ventilation (APRV) was initially described in 1987 by Stock and colleagues as a groundbreaking form of mechanical ventilation. Instead of delivering tidal volume by elevating airway pressure above the positive end-expiratory pressure (PEEP), APRV entails the provision of continuous positive airway pressure with a brief intermittent release phase, enabling the release of only a partial lung volume and allowing spontaneous breathing throughout the high-pressure phase [16]. Theoretically, in the context of heterogeneous lung injury under APRV ventilation, the appropriate elevated baseline airway pressure (Phigh) at the safe target and prolonged duration of Phigh could optimally facilitate gradual alveolar recruitment over time, while averting overinflation. Moreover, the brief release phase (Tlow) allows for only a partial loss of lung volume to eliminate carbon dioxide, prevent alveolar collapse, and foster alveolar stability and homogeneity. Consequently, APRV emerges as an exemplary protective mechanical ventilation strategy for enhancing pulmonary function and mitigating lung injury [12, 17].

Animal experiments have illustrated that employing a physiology-driven approach to APRV, as opposed to low tidal volume ventilation (LTV), in ARDS animal models, enhances alveolar recruitment and gas exchange, mitigates lung injury, preserves surfactant protein and lung architecture, improves homogeneity without increasing lung stress and strain, and allows for spontaneous breathing [18–23]. This approach also decreases intrathoracic pressure, enhances systemic venous return, and mitigates the cardiovascular depressant effects of positive pressure [24–26]. Despite offering compelling physiological advantages over other ventilation modes, the clinical impact of APRV remains uncertain due to inconsistent outcome data, substantial heterogeneity in its application, and a dearth of convincing evidence [27].

In a single-center, randomized controlled trial, early physiology-driven APRV was compared with LTV in ARDS patients with a partial pressure of arterial oxygen and a fraction of inspired oxygen (PaO_2_/FiO_2_) ratio of ≤ 250mmHg [28]. The findings demonstrated that APRV significantly improved oxygenation and respiratory system compliance, reduced plateau airway pressure, decreased sedation requirement, and also led to hemodynamic improvement. A secondary analysis of existing data revealed that patients with moderate to severe ARDS derived greater benefit from mechanical ventilation with APRV than those with mild ARDS. To further investigate the early use of physiology-driven APRV in ARDS patients, our group has designed a multicenter randomized clinical trial to assess the impact of mechanical ventilation with APRV in patients with moderate-to-severe ARDS. This paper outlines the study procedures and planned analyses for this clinical trial, which is registered on ClinicalTrials.gov under number NCT03549910.

## Methods and analysis

### Trial conduct

We will procure informed consent from the legally authorized representatives. The trial has been approved by the Ethics Committee of West China Hospital of Sichuan University under approval number 2019 − 337, as well as the regional ethics committee of each participating site.

### Trial design

#### Study design

To test the hypothesis that early physiology-driven APRV ventilation will result in an improvement in the primary outcome of mortality until 28-day for patients with moderate to severe ARDS, we have developed a multicenter, prospective, randomized clinical trial (APRVplus trial). The overall study flow is depicted in Fig. 1.

**Fig. 1 Fig1:**
[figure not shown]
Study flow diagram

#### Study population

The study will enroll adult patients aged 18 years and older who have been admitted to the intensive care unit (ICU) with moderate to severe ARDS, have undergone tracheal intubation, and received invasive mechanical ventilation for less than 72 h. The Berlin Conference definition will be utilized to identify patients with moderate-to-severe ARDS, including (A) hypoxemic respiratory failure with a PaO_2_/FiO_2_ ratio < 200 mmHg, (B) bilateral alveolar infiltrates on chest X-ray not present for more than 7 days, (C) respiratory failure not fully explained by cardiac failure or fluid overload, and (D) intubation on controlled ventilation and receiving PEEP ≥ 5 cmH_2_O [29].

Patients will be excluded from the trial if they meet any of the following criteria: (a) age over 85 years, (b) pregnancy, (c) suspected vasculitic pulmonary hemorrhage, (d) neuromuscular disorders known to prolong the need for mechanical ventilation, (e) severe chronic obstructive pulmonary disease, (f) severe hemodynamic instability (mean arterial pressure less than 60 mmHg despite sufficient fluid administration and use of high-dose vasoactive drugs (equivalent vasoactive drug dose: norepinephrine > 1.0 µg/kg/min)), (g) intracranial hypertension, (h) acute coronary syndrome, (i) pneumothorax, subcutaneous emphysema, pneumomediastinum, or pneumatocele, (j) patients in a moribund state or receiving palliative care only, (k) consent not obtainable, or (l) patients previously enrolled in another study.

Patients will be recruited from roughly 35 clinical sites in Mainland China with expertise in the identification and treatment of ARDS. Research investigators will provide training to the sub-research group at each sub-center on research protocols and implementation procedures. Coordinators at each participating site will assess potential candidates for enrollment. Once a patient is eligible for the study, a research investigator will obtain informed consent from the surrogate decision-maker. Subsequently, eligible patients will be enrolled and randomized, and initial ventilator adjustments will be made within 6 h.

#### Randomization and blinding

After enrollment, patients will be randomized in a 1:1 ratio to either the APRVplus group or the LTV group using a block randomization scheme. The random allocation list was crafted by a statistician uninvolved in the clinical aspects of the trial, utilizing a computer-generated random number list. Randomization will be stratified by enrollment site, pulmonary ARDS, and extrapulmonary ARDS. Assignment schedules were generated for each participating site, and allocation concealment was assured through a central web-based system (APRVplus.com) managed by Sichuan Zhikang Tech Co., Ltd. The treatment allocation for each patient will only be disclosed after their enrollment in the study.

As the intervention will be administered to critically ill patients on mechanical ventilation, most of whom are sedated, patient blinding is deemed unnecessary. Given that this is a nonpharmacological intervention, blinding the medical team is not feasible. Since there is no requirement for a committee to validate the study endpoint (death), outcome evaluators will not be blinded. However, the statisticians responsible for the analyses will be kept blinded to treatment groups for the duration of the study.

### Intervention

#### Ventilation strategy prior to randomization

In both groups, the goals of mechanical ventilation were to maintain PaO_2_ between 55 and 100 mmHg or pulse oximeter between 92% and 98%, PaCO_2_ between 30 and 50 mmHg, an arterial pH between 7.30 and 7.45, and limit plateau pressures no more than 30 cm of water (cmH_2_O). All patients initially received volume-assisted control ventilation (A/C-VCV) in accordance with the LTV ventilation strategy outlined by ARDSnet [30], prior to randomization into the APRV group or LTV group. Initially, tidal volume (VT) was set at 6mL/kg of predicted body weight (PBW), and PEEP was determined using the FiO_2_/PEEP table. Subsequently, the optimal PEEP was further adjusted based on oxygenation or compliance, at the discretion of the clinician. PEEP was incrementally increased by 2 cmH_2_O every 10 min, with measurements of PaO_2_ or respiratory system compliance taken at each step. The optimal PEEP was identified as 2 cmH_2_O below the level at which either PaO_2_ or compliance decreased by more than 10%. Alternatively, PEEP levels were adjusted using the pressure-volume (P-V) tool, with the optimal PEEP typically defined as 2 cmH_2_O above the lower inflection point (LIP) [31]. Tidal volume adjustments were made as follows: if the plateau pressure (Pplat) exceeded 30 cmH_2_O at a VT of 6 ml/kg predicted body weight and arterial pH was greater than 7.2, VT was reduced to 4–6 ml/kg predicted body weight. If Pplat was lower than 25 cmH_2_O, and patients experienced frequent stacked breaths or severe dyspnea, VT was adjusted to 6–8 ml/kg. Respiratory mechanics, including plateau pressure (Pplat), airway resistance (Rrs), and static compliance (Cstat) during a 0.5-second inspiratory pause, were monitored at least twice daily and after any changes in PEEP or VT.

#### Ensure sufficient cardiovascular system blood volume before randomization

Before randomization, effective cardiovascular system circulating blood volume should be evaluated. If the blood volume is insufficient, volume expansion treatment should be given to avoid hypovolemia. For shock patients, rapid fluid resuscitation and, if necessary, combined with vasoactive drugs will be used to achieve MAP ≥ 60 mmHg as soon as possible.

#### APRV group

In the APRVplus group, during the transition from the original ventilation with VCV mode to APRV, the following initial settings were applied: the high airway pressure (Phigh) was set at the Pplat measured at the previous VCV settings, not exceeding 30cmH_2_O; the low airway pressure (Plow) was set at 5cmH_2_O, representing the minimal pressure level similar to physiological transpulmonary pressure, and used to prevent atelectasis in accordance with established practice. The target tidal volume was set at 6-8 ml/kg PBW, and the duration of the release phase (Tlow) was adjusted as follows: Step one: The initial setting was 1.0 ~ 1.5 τ (expiratory time constant), which equals the product of the static compliance of the respiratory system and airway resistance (measured in lung volume unit L); Step two: Tlow was adjusted according to the expiratory flow-time curve, ensuring that the end-expiratory flow rate was ≥ 75% of the peak expiratory flow rate (PEFR); Step three: If the tidal volume was < 6 ml/kg PBW and patient-ventilator asynchrony occurred, Tlow was gradually extended, ensuring that the minimum end- expiratory flow rate was at least > 50% of PEFR; the release frequency was set at 10–14 frequency/min, or referenced to the original respiratory rate; the duration of Phigh (Thigh) was indirectly calculated based on Tlow and the release frequency. Initially, the spontaneous respiratory level was targeted as spontaneous minute ventilation (MVspont), approximately 30% of the total minute ventilation (MVtotal): severe ARDS (the ratio of PaO_2_: FiO_2_ < 100): MVspont less than 20% MVtotal, absent of dyspnea; mild to moderate ARDS (the ratio of PaO_2_: FiO_2_ > 100): MVspont: 20 ~ 60% of MVtotal, RR ≤ 35 times/min, no signs of respiratory distress.

Throughout the period of APRV ventilation, the APRV settings were adjusted based on the expiratory flow-time curve, lung mechanics and ventilation parameters, spontaneous breathing ventilation level, analgesia and sedation depth, patient-ventilator interaction, and arterial blood gas results, ensuring effective CO_2_ removal (PaCO_2_ 30 ~ 50mmHg) and adequate oxygenation (PaO_2_ 60 ~ 100mmHg). (For details on the APRV settings for titration, see Appendix).

#### Control group

In the control group, the upper limit for Pplat is set at 30 cmH_2_O, and the driving pressure is constrained to a maximum of 14 cmH_2_O. The target VT is 6 mL/kg PBW, and PEEP is adjusted based on optimal oxygenation, compliance, or P-V tool, with the flexibility to adjust VT within the range of 4–8 mL/kg PBW to prevent alveolar overextension and minimize patient-ventilator asynchrony. Specifically, in patients with a VT of ≥ 6 ml/kg PBW, the driving pressure exceeding 14 cmH_2_O and the Pplat above 25 cmH_2_O, or a Pplat exceeding 30 cmH_2_O with arterial pH greater than 7.2, VT is adjusted within the range of 4-6 ml/kg. VT can be gradually reduced in small decrements (e.g., 0.5 ml/kg PBW) over 1 h. Throughout the process of reducing VT, individual patient responses indicating intolerance to lower VT, such as tachycardia, hypotension, tachypnea, patient–ventilator dyssynchrony (e.g., double triggering), inspiratory airway pressure below PEEP indicating excess work of breathing, respiratory acidosis, and hypoxemia despite high FiO_2_, should be closely monitored over several hours. If signs of intolerance develop, adjunctive therapies, such as deep sedation, neuromuscular blockade or ECCO_2_R, should be considered to facilitate tolerance of low VT.

In cases of severe respiratory acidosis (pH<7.15), the respiratory rate was increased to 35 breaths per minute, with adjustments made in VT (Pplat target of 30 cmH_2_O may be exceeded), following the ARDSnet protocol. If severe respiratory acidosis persisted (pH<7.15), NaHCO_3_ could be administered.

If the PaO_2_:FiO_2_ ratio is less than 200 with FiO_2_ ≥ 0.5, the optimal PEEP should be checked using the above methods. If oxygenation does not improve, clinicians should assess and treat non-pulmonary causes of hypoxia, ruling out reversible causes and ensuring fluid optimization. In the presence of hypotension (mean arterial pressure less than 60mmHg) and pneumothorax occurrence with or without chest tube drainage, the clinician may modify PEEP levels according to the individual patient’s needs.

#### Recruitment maneuver

If the above interventions fail and patients without focal ARDS have been ventilated for less than 7 days, a stepwise recruitment maneuver can be performed. PEEP is increased in 5 cmH_2_O increments, allowing 30 s per step, until peak inspiratory pressure reaches 40 cmH_2_O, and then 40 cmH_2_O of pressure amplitude is applied for 40 s. In the descending period, PEEP is decreased by steps of 2 cmH_2_O every 5 min, and PaO_2_ or respiratory system compliance is measured at each step. The optimal PEEP is defined as 2 cmH_2_O above the level of PEEP where PaO_2_ or respiratory system compliance drops by more than 10% [32]. After the PEEP is set at the optimal level, a second recruitment maneuver is applied. If the PaO_2_:FiO_2_ ratio or respiratory system compliance increases by less than 10%, the recruitment maneuver should be stopped, and adjuvant therapies should be considered. For recruitment maneuver during APRV ventilation, Phigh and Plow were simultaneously increased in 5 cmH_2_O increments (allowing 30 s/step) until Phigh at 40 cmH_2_O, and then 40 cmH_2_O of pressure amplitude was applied for 40 s. In the descending period, Phigh and Plow were decreased by steps of 2 cmH_2_O/4 min and PaO_2_ was measured at each step. The optimal Phigh and Plow was defined as 2 cmH_2_O above the level of pressure, where PaO_2_ dropped more than 10%. After the optimal P high and Plow were set at the optimal level, a second recruitment maneuver was applied. If the PaO_2_:FiO_2_ ratio or respiratory system compliance increases by less than 10%, the recruitment maneuver should be stopped, and adjuvant therapies should be considered.

#### Co-interventions

Both intervention groups will receive standard analgesic and sedative treatment to ensure patient comfort while achieving the desired level of analgesia and sedation. The analgesia target level will be determined by the Critical-care pain observational tool (CPOT) score of 0 ~ 2 [33]. The sedation goal will be targeted as the Richmond Agitation Sedation Scale (RASS) score of -2 to 0 [33]. In the control group, clinicians will titrate the ventilator settings and the administration of analgesic and sedative drugs to achieve the optimal patient-ventilator interaction and sedation goal. In the APRV group, clinicians will adjust APRV settings and the dosages of analgesic and sedative drugs to achieve the desired level of spontaneous minute ventilation, analgesia, and sedation. If patients still exhibit anxiety, agitation, or respiratory distress after the ventilator settings have been optimized, deeper sedation (RASS scale < -2) will be administered.

As per usual sedation procedures, nurses will continuously monitor the depth of sedation and adjust the dosages of analgesic and sedative drugs to maintain the target level of analgesia and sedation. RASS scores will be recorded every 4 h (or more frequently when indicated) by the nursing staff to ensure accurate titration of the sedative infusion.

#### Adjuvant interventions for persistent hypoxemia

In cases of persistent severe hypoxemia (with no response to the assigned protocol and a PaO_2_:FiO_2_ ratio of < 150 mmHg during invasive mechanical ventilation for at least 12h), clinicians may consider implementing adjuvant interventions for hypoxemia at their discretion, such as prone positioning, neuromuscular blockade, or inhalation of nitric oxide, in both groups [34].

1) Prone positioning: If there are no contraindications, prone positioning can be performed for more than 12 h per day after careful preparation, following the criteria outlined by Guerin C, et al. [35]. Exclusion criteria for prone positioning include unstable spine, uncontrolled intracranial pressure, open abdominal injury, multiple trauma with skeletal/cervical traction, pregnancy, intra-abdominal pressure ≥ 20 mmHg, and severe hemodynamic instability.2) Neuromuscular blockade: a If Pplat exceeds 30 cmH_2_O, and spontaneous inspiratory efforts are clinically detected, neuromuscular blockade is indicated. b Despite prioritizing optimization of ventilator settings, if patients exhibit rigorous respiratory effort, dyspnea, or breath stacking, neuromuscular blockade may be employed to prevent lung injury and facilitate smooth adaptation between the patient and the ventilator.3) Inhalation of nitric oxide: If patients do not respond to the above therapies and continue to experience severe hypoxemia with a PaO_2_/FiO_2_ ratio < 150 and an increase in pulmonary artery pressure, administration of 5–20 ppm iNO with concentration may be considered, with reassessment 48h later.

All adjuvant interventions are utilized at the discretion of the clinician. Once the treatment goal of PaO_2_/FiO_2_ > 150 mmHg with FiO_2_ < 0.6 is achieved, clinicians may discontinue these interventions. If patients do not respond to the adjuvant interventions, the clinician may consider initiating ECMO.

#### Other treatments

During the treatment of ARDS, clinical doctors should manage patients according to best clinical practice evidence, closely and dynamically evaluate and solve pulmonary and extrapulmonary factors that cause or exacerbate hypoxia, such as anti-infection, optimized fluid therapy, maintaining appropriate hemoglobin levels, and optimize balance of oxygen supply and demand, actively prevent and treat complications.

### Weaning from mechanical ventilation

#### Weaning protocol in the LTV Group

Commencing the day after enrollment, patients in the LTV group will undergo a daily spontaneous awakening trial (SAT) followed by a spontaneous breathing trial (SBT) throughout the mechanical ventilation period [36]. If patients are under deeper sedation (RASS score < -2), they will be evaluated every morning by physicians using a daily SAT safety screen. In the absence of contraindications, such as severe hypoxemia, myocardial ischemia, hypertensive crisis, status asthmaticus, sustained agitation with increased use of sedation drugs, or treatment with neuromuscular blockers, patients will undergo an SAT trial, and sedative and analgesic infusions will be stopped until the patients are awake [37]. Analgesics for active pain will be continued. The awakening criteria include the ability of patients to perform three simple tasks: opening their eyes, squeezing the hand and moving fingers, and expressing discomfort [38]. If patients experience sustained agitation, marked dyspnea, SPO_2_ < 88% for ≥ 5 min, or arrhythmias, it is considered SAT failure. In such cases, bedside nurses will restart analgesics and sedatives at half the previous dose and titrate the medications to achieve the target sedation range [37]. These patients will be reassessed the following morning.

For patients under light sedation (RASS score of -2 to 0), sedative and analgesic infusions will be discontinued, while analgesics for ongoing pain management will be maintained. Patients who pass the SAT or those with RASS scores − 2 to 0 who have interrupted sedation will immediately undergo the SBT protocol. Respiratory therapists will manage patients with the SBT safety screen, and those who pass the criteria will undergo a 30-minute SBT trial with pressure support ventilation of 5–8 cmH_2_O, PEEP of 5 cmH_2_O, and FiO_2_ of ≤ 40% [39]. If the SBT trial is successful, physicians and respiratory therapists will decide on extubation. If the SBT is unsuccessful, pre-weaning settings will be resumed, and the patients will be reassessed the following morning.

The SBT safety screen criteria include improved cause of respiratory failure, FiO_2_ ≤ 0.40, PEEP ≤ 8 cmH_2_O, PaO_2_ ≥ 60 mmHg, acceptable spontaneous breathing efforts, systolic BP ≥ 90 mmHg, no significant use of vasopressors, and no neuromuscular blocking agents [37]. Successful tolerance for the SBT trial for up to 30 min is determined by specific criteria, including SpO_2_ ≥ 90% and/or PaO_2_ ≥ 60 mmHg, spontaneous VT ≥ 4 ml/kg PBW, respiratory rate ≤ 35/min, pH ≥ 7.3, hemodynamic stability (heart rate and blood pressure changing less than 20% from the previous level, or absence of acute cardiac arrhythmia), and absence of respiratory distress, such as respiratory rate exceeding 120% of baseline, significant accessory muscle use, abdominal paradox, diaphoresis, or pronounced dyspnea [39].

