#### Weaning protocol in the APRV Group

1) First Stage: Once the goal for oxygenation has been achieved, FiO_2_ is gradually reduced to ≤ 0.6, followed by a stepwise decrease in Phigh by 1–2 cmH_2_O to ≤ 26 cmH_2_O, unless the patient’s oxygenation deteriorates.2) Second Stage: After the improvement in the cause of respiratory failure, if pH ≥ 7.3, PaO_2_ > 70mmHg, SaO_2_ > 92%, FiO_2_ ≤ 40%, PaO_2_/FiO_2_ ≥ 200, Phigh is gradually and simultaneously reduced by 1–2 cmH_2_O and the release rate by 2 frequency twice daily unless the patient’s cardiopulmonary function deteriorates. Patients under deeper sedation (<-2) will have gradual and simultaneous reductions in analgesia and sedation based on the spontaneous minute ventilation target level and sedation goals combination.3) Third Stage: When patients achieve the criteria with Phigh ≤ 20 cmH_2_O and FiO_2_ ≤ 40%, they will undergo the daily SBT trial, similar to the weaning protocol in the LTV group.

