#### Outcome

The primary outcome measure is mortality until day 28. Secondary outcome measures include physiological parameters at baseline, day 1, 3, and 7, encompassing ventilator settings and monitoring parameters, pulmonary mechanics such as plateau airway pressure, respiratory system compliance (Crs), and gas exchange parameters such as PaO_2_ and PaCO_2_. Additional variables include hemodynamic parameters, urine output, fluid balance, laboratory findings, and details regarding the dosage and type of sedatives and analgesics, vasopressors, lung recruitment maneuvers, and adjuvant therapies such as prone positioning, nitric oxide therapy, paralysis, and continuous renal replacement therapy. Outcome measures will encompass mechanical ventilation duration, ventilator-free days at day 28, ICU and hospital length of stay, rate of successful extubation, rate of tracheostomy, ICU and hospital mortality. Furthermore, any adverse events occurring during the study period, including barotrauma, ventilator-associated pneumonia, and other complications related to mechanical ventilation, will be collected and analyzed.

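### The rule for passing a spontaneous breathing trial joins its two hemodynamic conditions with *or* where *and* is needed, so neither a large pressure or heart-rate change alone nor a new arrhythmia alone counts as unstable

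*Protocol article*

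**What the plan says.** The SBT success criteria are in the protocol article under Weaning protocol in the LTV Group. They cover oxygenation, spontaneous tidal volume, respiratory rate, pH, hemodynamics and respiratory distress. The hemodynamic item is stability, defined in brackets as "heart rate and blood pressure changing less than 20% from the previous level, or absence of acute cardiac arrhythmia". The respiratory item that follows it requires "absence of respiratory distress, such as respiratory rate exceeding 120% of baseline, significant accessory muscle use" and further signs, the last of them joined by *or*.

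The safety screen that a patient must pass before starting an SBT includes "systolic BP ≥ 90 mmHg, no significant use of vasopressors".

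On the consequence of passing, the same section says: "If the SBT trial is successful, physicians and respiratory therapists will decide on extubation". After an unsuccessful SBT the patient returns to the earlier settings and is reassessed the next morning.

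In the other arm, patients who reach the third weaning stage follow the same kind of test: "they will undergo the daily SBT trial, similar to the weaning protocol in the LTV group".

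**The concern.** A list of failure signs and a list of success conditions need opposite connectors. If any one sign is to fail the test, the failure list uses *or* and the success list must use *and*. The hemodynamic item is a success list with the connector of a failure list. Read as written, it calls a patient stable when only one of the two conditions holds.

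The SBT result decides whether a patient goes forward to the extubation decision that day or waits until the next morning. A team that applies the words literally sends forward a patient with a marked pressure or heart-rate change, or with a new arrhythmia. A team that reads *or* as *and* holds the same patient back. At stake are the safety of that step and the comparability between sites of the secondary outcomes that depend on it, listed under Outcome as "mechanical ventilation duration, ventilator-free days at day 28, ICU and hospital length of stay, rate of successful extubation".

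**Working it through.** The protocol states no figure for this clause, so there is none to reproduce. The check is on the logic.

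**Step 1. Truth table.** Let A be a heart-rate and blood-pressure change of less than 20%, and B the absence of an acute arrhythmia.

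| A | B | Clinical picture | As written (A or B) | With *and* (A and B) |
|---|---|---|---|---|
| yes | yes | neither sign | stable | stable |
| yes | no | arrhythmia alone | stable | unstable |
| no | yes | change of 20% or more alone | stable | unstable |
| no | no | both signs | unstable | unstable |

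The written rule accepts three of the four combinations and *and* accepts one, so two are judged differently. These are logical cases, not patient frequencies.

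**Step 2. Example (values chosen for illustration).** Systolic pressure falls from 112 to 84 mmHg with no arrhythmia: (84 − 112) / 112 = −25%. A fails and B holds, so the clause is met. Yet at 84 mmHg this patient could not have started the SBT, because the safety screen requires at least 90 mmHg.

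**Step 3. Does another criterion catch these patients?** The remaining success criteria concern SpO2 or PaO2, tidal volume, respiratory rate, pH and respiratory distress. None names blood pressure, heart rate or rhythm. The article gives no separate SBT failure rule that would correct the clause.

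**Step 4. What was probably meant.** The respiratory item in the same sentence demands the absence of every sign in its list, so a respiratory rate above 120% of baseline disqualifies on its own. The hemodynamic item lists conditions that must hold, so the same connector has the opposite effect. The rule for the spontaneous awakening trial (SAT) points the same way: "If patients experience sustained agitation, marked dyspnea, SPO_2_ < 88% for ≥ 5 min, or arrhythmias, it is considered SAT failure". There an arrhythmia alone is failure. The SAT is a different test, so this is only a hint.

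**Step 5. Size, under stated assumptions.** Among patients with a change of 20% or more, the share still counted as stable is 1 − P(arrhythmia given such a change). The article gives no arrhythmia rate. At an assumed 1%, 3% or 10%, the share is 99%, 97% or 90%.

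How often the two readings differ also depends on how common such changes are, which is not given either. For illustration, let the percentage changes in heart rate and pressure be bivariate normal with equal means and SDs and correlation 0.3, with arrhythmia independent of them. With q = P(either changes by 20% or more) and a = P(arrhythmia):

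- P(pass with *or*) = 1 − q·a
- P(pass with *and*) = (1 − q)(1 − a)
- discordance = q(1 − a) + (1 − q)a

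| Assumed mean, SD (%) | a | q | Pass, *or* | Pass, *and* | Discordant |
|---|---|---|---|---|---|
| 0, 8 | 1% | 0.024 | 0.9998 | 0.966 | 0.034 |
| 5, 12 | 1% | 0.223 | 0.998 | 0.770 | 0.228 |
| 10, 15 | 3% | 0.448 | 0.987 | 0.535 | 0.452 |

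If arrhythmia instead occurs in 10% of patients with a large change and 1% of the others, discordance is 0.032, 0.208 and 0.409. These are clause-level figures and so upper bounds for the SBT result. If half of the discordant patients fail another criterion, which is again an assumption, the three figures in the table become 0.017, 0.114 and 0.226.

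**The case against.** The governing term is hemodynamic stability, and the bracket only explains it. Few bedside teams would call a patient stable with a new acute arrhythmia, or with a pressure down 25% to 84 mmHg. The intended meaning can be recovered from the same sentence, so this is close to copy-editing.

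There are also safeguards. The list of criteria is open, because it is introduced as inclusive. Passing does not trigger extubation, since clinicians decide afterwards. The Discussion describes training on both ventilation protocols, scenario-based tests and continuing guidance from the lead centre. Nothing in the article shows that any site applies the literal reading. The discordance rates rest wholly on assumed inputs, span more than a tenfold range, and compare two readings each applied by everyone. The true effect must be scaled by the share of teams that read the clause literally, which may be near zero.

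Most of this stands, and it keeps the point small. The rates illustrate and prove nothing about size, and the conclusion does not rest on them. What the objection does not do is repair the rule. A written criterion exists so that sites need not supply the right meaning themselves, and the described training does not mention the SBT criteria. Nor is the literal reading far-fetched: the same sentence offers SpO2 and PaO2 as genuine alternatives.

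**Conclusion.** The clause is wrong as written. Instability requires both a change of 20% or more and an arrhythmia, and nothing else in the article corrects it. This follows from the text alone and needs no assumption. That *and* was meant is an inference from the surrounding rules, but a strong one.

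The importance is low. It is a patient-safety and consistency point about a bedside rule used in both arms, and it bears on secondary outcomes only. No effect is claimed on 28-day mortality, sample size or power. Both arms use a similar SBT and randomization is stratified by site, so differences in reading between sites should largely balance across arms. The practical frequency is unknown: it depends on how often such changes and arrhythmias occur during SBTs, how many of these patients fail another criterion, and how many teams follow the words literally.

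**What to change.** In the SBT success criteria, change the connector so that hemodynamic stability requires a heart-rate and blood-pressure change of less than 20% from the previous level *and* no acute cardiac arrhythmia. State that the same criterion governs the SBT in the APRV arm, whose weaning section only refers back to the LTV protocol, and send the sites a short note.

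The cost is a one-word clarification, processed as the section on protocol amendments requires. SBTs already judged may have used the looser reading and cannot be re-run. With completion expected by the end of December 2024, the change helps only patients still to be weaned. Applied to both arms at once, it should not favour either.
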